### Enrollment, retention, and tracking

The names and identification numbers (IDs) of participants who consent to become involved will be entered into a tracking form. IDs will be substituted for names on all questionnaires and study forms. Confidentiality of data will be assured by maintaining locked file cabinets and protected electronic files that require a password. The PI and project coordinators will be responsible for maintaining IDs and data files. We have created a tracking system using established strategies [43]. The investigative team has considerable experience with recruitment and retention of transition-age youth with serious mental health conditions in a variety of settings, and with individuals in poverty experiencing multiple stressors. Our strategies have resulted in high retention rates (90 %) in our previous studies [4, 44]. We will use these experiences to implement the tracking system and to help minimize logistical barriers for participation. Furthermore, some of the young people targeted for enrollment will already be receiving care at the clinic. Due to the close relationship between the staff and the investigators, we anticipate few participants will be lost to follow-up. Keeping a list of participant names, addresses, phone numbers, and contacts will enable us to make phone calls and send appointment reminders in an effort to maintain engagement. We will also ask each participant on a regular basis to update their phone numbers and addresses so that we have alternative ways of reaching them. This tracking system will be locked in a separate file cabinet from all study data that will only be identified by a study ID number. Based on our experiences, we do not anticipate many participants will be lost due to relocation. We are recruiting 60 transition-age youth (TAY) to achieve a final sample size of 55.

Addressing within-group randomization and potential for contamination: in the proposed study the experimental/control assignment will be done within site and therefore issues of potential contamination must be addressed. Our research has revealed that we must consider contamination on both the participant and the provider level(s). It is possible that the participants may discuss their involvement in Cornerstone with another young person who is in the control condition. However, we expect this to be minimal as these young people do not typically have involvement with each other either within or outside the outpatient clinic site. Contamination at the provider level is of some concern as well. It is possible that the Cornerstone staff might share materials from Cornerstone manuals and trainings; however, the facilitation skills require practice and supervision to incorporate the services into overall care. Thus, contamination at this level will be minimal. We will take precautions by asking providers not to share materials and information until the study is over and explaining why this is important. We will also remind providers during our regular project meetings of this sensitive issue. We will also collect data to assess the nature and degree of contamination by asking providers if they have discussed Cornerstone content with colleagues, and if so have they noticed service changes as a result of discussions.

### Measures

Most of the measures proposed in the study have been piloted with the target population and have been found to have good psychometric properties. We are also including a few measures in the battery in order to examine their psychometric properties, as a cost-effective strategy in preparation for their use in future studies. Table 2 presents a summary of the major study measures and their psychometric characteristics. These measures include factors we hypothesize are going to make the greatest impact.

**Table 2 Tab2:** Measures for Cornerstone randomized trial

Construct and dimension (corresponds with Fig. 1)	Instrument category and name	Psychometric properties	Timing
Mediating outcomes			
Image impressions stigma	Stigma subscale of the Inventory of Attitudes Toward Mental Health Services, IASMHS [52]	8-item, Likert scale 0 to 4; strong validity and reliability with youth (α = 0.83) [53, 54]	B, 3, 6, 9
Behavioral beliefs mistrust	Group-Based Mistrust Scale [55]	12-item, Likert scale 1 to 5; strong validity; alpha = .91 [55]	B, 3, 6, 9
Self-efficacy	Efficacy: Perceived Behavioral Control Measure [56]	7-item scale; strong internal consistency [Factor 1 ease, α = 0.78, Factor 2 control, α = 0.60)	B, 3, 6, 9
Outcomes			
Intention to engage services	Behavioral intention: utilized in decision-making (intend to attend therapeutic sessions as scheduled)	Standardized scales developed and tested over 20 years by Fishbein et al., Likert scale 1 to 5 [56]	B, 3, 6, 9
Mental health service use			
Attendance	Behavioral outcome: group attendance sheets (standardized sheets)	Utilized in pilot study	Bi-weekly
Adherence to services	Behavioral outcome: tracking system, youth self-report and clinician report: Medication and appointments: “How often do you keep your appointments for this service?”	Strong face validity; utilized in studies of adherence of youth [57] Responses: (0) all of the time (1) most of the time, (2) a moderate amount of the time, (3) sometimes (4) never or almost never.	B, 3, 6, 9
Mental health			
Recovery measure	Mental Health: Recovery Assessment Scale-Short Form [58]	Study of reliability of recovery measure [59]	B, 3, 6, 9
Depression symptoms	Mental Health: Center for Epidemiological Studies Depression Scale (CES-D) [60]	20-item, high internal consistency and test-retest reliability, and validity [61]	B, 3, 6, 9
Perceived stress	Mental Health Outcome: Global Measure of Perceived Stress [62]	14-item, Likert scale, 1 (never) to 5 (very often), reliability (0.75) [62]	B, 3, 6, 9
Mental Health in Action Outcomes – Each outcome includes a continuous measure of perceived importance			
Natural supports	Life outcomes items on presence of social support relationships Example of the perceived importance measures [63]	“Do you have natural supports in your life?” [Interviewer reads list] i.e., “How important is it to you to have natural supports in your life?”	B, 3, 6, 9
Housing	Life outcomes items on housing, current residence [64]	Where are you currently living?	B, 3, 6, 9
Young adult employment/education	Life outcomes current work and/or education, residential status	Items utilized in previous research with transition-age youth [64]	B, 3, 6, 9
Social/community Inc.	Life outcomes social inclusion [65] Life outcomes community integration [66]	How many times in the last 7 days have you …e.g., visited in person with a friend or friends?	B, 3, 6, 9
Maintaining insurance	Life outcome maintaining health insurance	Do you currently have health insurance?	B, 3, 6, 9
Additional measures			
Cornerstone Fidelity	(1) Cornerstone session content items	6-items	6 mo. interview
Implementation Checklist	The BSCM and RRM will be asked for this information via a checklist	Barriers: (1) time; (2) transportation and; (3) staffing.	Aim 3 interview

*BSCM* boundary-spanning case manager, *RRM* recovery role model

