### Barriers to engagement

Research has identified barriers to mental health service use among transition-age youth, for example, lapses in insurance, mistrust, and stigma, among others [7]. For example, the belief that there is stigma associated with participating in treatment remains common among transition-age youth with mental health conditions, [14, 15] and it may play a role in the reluctance to continue treatment [16]. Also, studies have found that a lack of understanding and knowledge, sometimes referred to as ‘mental health literacy,’ of mental health and treatment can be a significant barrier to service use [17]. Further, these young people report that pessimistic messages from providers, irrelevant services, and mistrust are barriers to treatment continuation [18–20]. While the Affordable Care Act (ACA) can expand coverage for young adults, if implemented, without attention to perceptual obstacles that may be part of young adults’ beliefs, along with negative affective associations, continuous care is unlikely to be achieved. Such barriers must be addressed if we are to minimize dropout, increase investment, and improve long-term health and functioning outcomes of transition-age youth with SMHC.

In sum, the present article provides a description of the background, theoretical framework, protocols and the study aims for this intervention development trial, which will refine and examine the feasibility, acceptability, and preliminary impact of a theoretically guided intervention focused on improving the mental health, service use, and young adult life outcomes of low-income individuals with SMHC. The project will develop revised manuals (i.e., treatment, training, and implementation) and protocols with enhanced ‘real world’ validity in the mental health clinical context, and test its preliminary efficacy among transition-age youth with SMHC.

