Data analysis for aim 2: due to limited sample size we will proceed cautiously to conduct basic omnibus analyses to examine whether Cornerstone leads to improved outcomes relative to TAU, as this study is intended for intervention feasibility and acceptability testing, and therefore we will conduct only exploratory statistical testing of study outcomes. Our primary goal in this proposal is to gather preliminary data to inform a future large-scale, fully powered, randomized control trial of Cornerstone [51]. For each study subject we will calculate the difference, relative to baseline, at the end of the study for each outcome specified (see Table 2 above). A simple *t* test will be used to assess whether these changes differ across treatment conditions. For example, we will examine whether the mean within-person difference between the 9-month assessment and baseline assessment of intention to use services differs for subjects in Cornerstone versus those in TAU. We will likewise examine whether within person changes in the proposed mediating variables differ across intervention groups.

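### Maintaining insurance is asked at four interviews but analysed only as end of study minus baseline, so a lapse that resolves in between counts as no change

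*Protocol article*

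**What the plan says.** In the protocol article, Measures, Table 2, the construct is named "Life outcome maintaining health insurance". The item is "Do you currently have health insurance", with timing at baseline, 3, 6 and 9 months. It is a yes/no question about the day of the interview, put four times.

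The Analysis section, under aim 2, fixes one contrast for everything in that table: "For each study subject we will calculate the difference, relative to baseline, at the end of the study for each outcome specified". A t "test will be used to assess whether these changes differ across treatment conditions". The worked example is "the mean within-person difference between the 9-month assessment and baseline assessment of intention to use services". No use is stated for the 3- and 6-month answers.

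The Background, under Barriers to engagement, gives as examples of barriers to service use "lapses in insurance, mistrust, and stigma, among others". The Abstract says medical records will be used to check self-report on diagnosis, treatment planning and attendance; insurance is not in that list.

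**The concern.** Maintaining cover is a statement about continuity, whereas the planned contrast compares two days about nine months apart. Code cover as 1 and no cover as 0. A participant insured at both ends scores 0, whether cover was unbroken or was lost and regained in between. The interrupted pattern is the kind of event that the Background names as a barrier to care, and the planned score cannot tell it from success. A participant who was uninsured at baseline and gains cover scores +1, which is acquiring cover rather than keeping it.

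What is at stake is limited. The 3- and 6-month interviews already collect most of the information needed, and the plan as written leaves it unused. If Cornerstone shortened or prevented temporary gaps, the stated analysis could miss that, and the pilot would hand a less informative measure to the larger trial it is meant to inform.

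**Working it through.** **Plan's own figures.** The plan gives no figure for lapses in cover. Its only aim 2 calculation is 80% power with 30 per group and d = 0.73. That reproduces at two-sided 0.05 (79.4% by the exact t test, 80.7% by the normal approximation). Nothing below depends on it.

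**Inputs from the documents.** Interviews at months 0, 3, 6 and 9 (Table 2); contrast of end of study minus baseline (Analysis, aim 2).

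**Assumptions, not in the documents.** The participant is insured at baseline and has one lapse. It starts at a time S uniform on 0 to 9 months and lasts L months. Interviews are on time and complete.

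**Planned contrast.** The lapse is visible only if it is in progress at month 9, that is, if S lies between 9 − L and 9. Probability = L/9.

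**All follow-up answers.** The lapse is visible if it is in progress at month 3, 6 or 9. Each interview catches starts in the L months before it, and these windows are 3 months apart. Probability = min(1, 3L/9) = min(1, L/3).

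| Lapse length L (months) | Planned contrast, L/9 | Months 3, 6 and 9, min(1, L/3) |
|---|---|---|
| 1 | 1/9 = 11% | 1/3 = 33% |
| 2 | 2/9 = 22% | 2/3 = 67% |
| 3 | 3/9 = 33% | 100% |
| 4.5 | 4.5/9 = 50% | 100% |
| 6 | 6/9 = 67% | 100% |

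A simulation of 1,000,000 lapses agrees with both formulas.

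**Lapses that start and end inside the 9 months.** Here S is uniform on 0 to 9 − L. The planned contrast sees 0% at any length. The 3- and 6-month answers see 2L/(9 − L) up to L = 3: 2/8 = 25% for 1 month, 4/7 = 57% for 2 months, 6/6 = 100% for 3 months, and 100% beyond that.

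**Varying lapse length.** If L is exponential with mean 1, 2, 3 or 6 months, the planned contrast sees 11%, 22%, 32% and 52%; all follow-up answers see 32%, 52%, 63% and 79%.

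**Late final interview.** The Interview protocol section allows the post-test at about 9 to 12 months. With interviews at 3, 6 and 12 months and S uniform over 12 months, the planned contrast sees L/12 (8%, 17% and 25% for 1, 2 and 3 months) and all follow-up answers see 3L/12 (25%, 50% and 75%). So the result that every lapse of 3 months or more is caught holds only if the last interview falls at 9 months.

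**The case against.** **Table 2 is a summary in a condensed article.** The full questionnaire may ask more about insurance. That is possible, and it would reduce the need for a new question. It does not change the contrast, which the Analysis section states for each outcome in the table.

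**The outcome is peripheral and exploratory.** Insurance is not one of the three mediators in the Conceptual framework. Outcome testing is declared exploratory, and the main goal is feasibility and acceptability in 60 youths. This stands, and it is why the point is minor.

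**Three stronger readings that a reader might infer do not hold.**

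- *The trial cannot show whether Cornerstone helps youth keep insurance.* Cover at the final interview, compared by arm, is a valid randomised comparison, and any loss that persists to that visit is visible in it. What the planned contrast lacks is continuity in between.
- *Lapses are mostly invisible.* For the planned contrast this depends on lapse length, which the documents do not give: more than half are missed below 4.5 months and fewer than half above. It is not true of the collected data as a whole. With interviews at 3, 6 and 9 months, more than half of lapses longer than 1.5 months are caught (L/3 > 1/2). The loss is mainly in the analysis rather than in the question.
- *Housing has the same defect, because its row shows the question* "Where are you currently living". That row refers to items in the plural and cites a source, so it is not established that this is the only housing question. A changed answer between interviews could also show a move.

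**Conclusion.** The point holds in a limited form. The stated analysis leaves the 3- and 6-month insurance answers unused and scores any lapse resolved before the final interview as no change. That a resolved lapse scores zero needs no assumption. How many lapses this affects does need one: with uniform start and lapse lengths of 1 to 6 months, the planned contrast sees 11% to 67%, against 33% to 100% with all follow-up answers. Sustained loss of cover is visible under either approach. This is a minor improvement to one exploratory outcome; it does not threaten the trial's main aims.

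**What to change.** 1. Keep the planned comparison of current cover. It can be completed for everyone and it captures sustained loss.
2. Add a by-arm comparison of any time without cover during follow-up, defined as at least one negative answer at 3, 6 or 9 months among those insured at baseline. Baseline cover should be recorded before the condition is known, so that this subset is fixed independently of arm. State how many had all three answers. This needs no new data.
3. For interviews still to come, add one question: *Since your last interview, was there any time you had no health insurance?* It covers the time between interviews, including the lapses shorter than 3 months that the current-status question often misses.

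**Cost.** Step 2 is one extra line in the analysis. Step 3 needs a minor IRB amendment and brings recall error over about 3 months. The Trial status section reports 30 of the 60 already enrolled, so look-back will be incomplete for any of them whose follow-up interviews are already done. The look-back result should therefore supplement the current-status comparison, not replace it.

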### Interview protocol

#### Timing of assessment and procedures

All participants will be interviewed by the research team at four time points: baseline (beginning of intervention), 3 months, 6 months, and post-test (approximately 9 to 12 months after baseline). The baseline and final interview will last approximately 90 minutes (compensation for participants time is $20/assessment) and the 3-month and 6-month follow-ups will last approximately 60 minutes. The interviews consist mainly of self-report questionnaires with some open-ended questions. The importance of honest responding will be stressed and a measure of social desirability response tendencies will be included for use as a covariate. There is debate about whether interviewer-administered questionnaires yield as truthful responses. If respondents are assured confidentiality, there is evidence to suggest that the differences in the two methods of assessment are minimal (e.g., [45]). Cornerstone participants will complete the assessments in planned meetings at the clinic. Structured and intensive interviewer training for the research staff will be conducted based on a training protocol. We estimate the training to require 8 hours of direct instruction and 4 hours of practice. Interviewer training will cover the following: (a) the research process and the clinic setting, (b) federal law regarding informed consent and the rights of research participants, (c) the basics of interviewing and the specifics of the project interview schedule, (d) coding interviews, (e) managing participant discomfort during and after an interview, (f) education about topics such as the psychosocial effects of poverty, trauma, mental illness and treatment, (g) desensitization to discussing poverty, trauma and mental illness, (h) interviewing participants from diverse cultural backgrounds, and (i) psychiatric interviewing. Then, weekly follow-up research staff meetings will be utilized to reinforce training and provide support throughout the trial.

### Methods for aim 3: the preliminary implementation study (phase 3)

All interviews on implementation (*n* = 20) will take place during months 30 through 36 of the grant period. These interviews will be conducted with key informants on the national, state, and local levels. Participants will include policy experts, clinic staff (i.e., administrators, clinicians, recovery role models), and experts on transforming payment structures. These interviews will follow a structured interview guide, but interviewers will be open to probing into new areas that emerge. The interview will focus on aspects important to implementation of a boundary-spanning intervention, such as planning, training, executing, and payment for services. We will combine the quantitative data from the checklists discussed above with the qualitative data from interviews to create a comprehensive review of factors that facilitate and impede implementation, along with a Cornerstone Implementation Manual that, if efficacious, will assist us in moving toward testing effectiveness of a much-needed intervention for transition-age youth.

### Analysis

Data analysis for aims 1 and 3: aims 1 and 3 involve qualitative data analysis, specifically grounded theory coding techniques [46, 47]. The qualitative data derives from in-depth interviews and group meetings. With participant permission, qualitative research activities will be recorded on digital audio recorders and in field notes. Analysis will proceed in two steps. Interviews will produce large volumes of text to be content analyzed. We will use a data-reduction process in which emergent themes are identified and coded to yield a set of core themes. Step 1 involves writing analytic summaries, concise reviews of key findings in each interview and field note. Analytic summaries will allow us to discuss key findings during project meetings. Step 2 involves systematic coding using a well-defined thematic codebook. Codebooks for qualitative analysis are theoretically informed manuals of codes and subcodes, defined by specific definitional criteria that allow for systematic textual coding. We will derive an analytic codebook based on the analytic summaries produced during step 1 and emergent themes. Trained coders and project staff will conduct all coding. All data will be analyzed using Atlas.ti, which will allow investigators to develop thematic units, or frequently occurring sets of explanatory statements [47]. In addition, the data will be explored for negative incidents and divergent themes vis-à-vis negative incident analysis [48]. With coded data in Atlas.ti, we will examine the range of variation of individual codes across our sample to obtain information about aggregate tendencies. This “vertical” analysis decontextualizes segments of data by removing them from the larger transcript, thereby permitting the examination of code-specific responses. Then, we will examine individual cases by analyzing how instances of particular factors are related to the larger context of meaning, experience, and behavior. This “horizontal” analysis allows us to examine how contextual factors may vary for transition-age youth with serious mental health conditions. We also will apply constant comparison coding methods throughout the project [49, 50]. Results will assist in modifying protocols and procedures at the local level, while also developing a Cornerstone Implementation Manual, and improved Cornerstone Intervention Manuals and Protocols.

Data analysis for aim 2: due to limited sample size we will proceed cautiously to conduct basic omnibus analyses to examine whether Cornerstone leads to improved outcomes relative to TAU, as this study is intended for intervention feasibility and acceptability testing, and therefore we will conduct only exploratory statistical testing of study outcomes. Our primary goal in this proposal is to gather preliminary data to inform a future large-scale, fully powered, randomized control trial of Cornerstone [51]. For each study subject we will calculate the difference, relative to baseline, at the end of the study for each outcome specified (see Table 2 above). A simple *t* test will be used to assess whether these changes differ across treatment conditions. For example, we will examine whether the mean within-person difference between the 9-month assessment and baseline assessment of intention to use services differs for subjects in Cornerstone versus those in TAU. We will likewise examine whether within person changes in the proposed mediating variables differ across intervention groups.

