**Methods/design:**

This study utilizes a hybrid research design and focuses on examining feasibility, acceptability and preliminary impact, along with factors that influence implementation, to maximize new knowledge. The study combines qualitative methods and a randomized controlled trial, using data to inform and refine protocols and manuals, while testing the preliminary impact of the intervention, compared to best available services (treatment as usual, TAU) at a partnering outpatient mental health clinic (*n* = 60). Contributors to the intervention development research (*n* = 20) are national experts on mental health services, clinic administrators and staff and young adults with direct experience. The intervention involves intensive staff training and 18 months of ongoing service provision, monitoring and supervision. Quantitative survey data will be collected at baseline, 3 months, 6 months, and 9 months measuring mental health and practical life outcomes via self-report measures. Medical records will be used to triangulate self-report data (i.e., primary diagnosis, treatment planning and attendance). Qualitative data focuses on the intervention development process and implementation research and will use constant comparison coding techniques. In this intention-to-treat analysis, we will conduct basic omnibus analyses to examine whether Cornerstone leads to improved outcomes relative to TAU utilizing *t* tests across treatment conditions for each outcome measure specified. We will likewise examine whether changes in the proposed mediating variables differ across groups.

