### Methods for aim 2: randomized trial of Cornerstone (phase 2)

Aim 2 will be accomplished with a two-group (random assignment, treatment versus control) by four-assessment (baseline, 3-month, 6-month, 9-month post) design. Participants will be involved for approximately 9 months. We will use an intention-to-treat design, thus, continuing to collect data on individuals who decide to drop out of the program before clinically indicated.

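### The aim 2 t test is labelled intention-to-treat, but as stated it is an available-case comparison of about 55 of 60, unadjusted for baseline and making no use of the 3- and 6-month scores

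*Protocol article*

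**What the plan says.** The abstract (Methods/design) announces the population and the method together: "In this intention-to-treat analysis, we will conduct basic omnibus analyses to examine whether Cornerstone leads to improved outcomes relative to TAU", by t tests on each outcome. The section on methods for aim 2 explains what the label means there: "We will use an intention-to-treat design, thus, continuing to collect data on individuals who decide to drop out of the program". The same section sets a two-arm design with assessments at baseline, 3, 6 and 9 months, and Table 2 lists nearly every self-report scale at all four.

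The Analysis section (data analysis for aim 2) defines the analysed quantity: "For each study subject we will calculate the difference, relative to baseline, at the end of the study". A simple t "test will be used to assess whether these changes differ across treatment conditions". The worked example uses the first and last visits only: "we will examine whether the mean within-person difference between the 9-month assessment and baseline assessment of intention to use services differs". The mediators are to be handled the same way.

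The section on enrollment, retention and tracking states the loss that the team expects: "We are recruiting 60 transition-age youth (TAY) to achieve a final sample size of 55".

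**The concern.** The difference is promised for every subject, but it cannot be formed for anyone without a final score. By the article's own numbers that is about 5 of the 60 randomised. The stated test and the label therefore do not match.

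The test also leaves aside information that the trial collects. The baseline score enters only by subtraction, which is inefficient unless baseline and final scores are very highly correlated. The 3- and 6-month scores, the best evidence on a participant lost after month 6, do not enter at all.

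Two things are at stake. One is the description of the analysed population, which would carry into the later powered trial that this pilot is meant to inform. The other is the precision of the 9-month contrasts with only 30 per arm. Bias is a third possibility: disengagement from services is the problem under study, so loss may be related to outcome.

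**Working it through.** **1. The article's own figure.** Inputs from the section on randomization and sample: 30 per group, d = 0.73, p = 0.05, 80% power. A two-sided two-sample t test (noncentral t) gives 79.4%, and the normal approximation gives 80.7%. The stated 80% is reproduced, and it assumes that all 60 have a change score. With the expected 55 (28 and 27), power is 75.7% and the effect detectable with 80% power rises from 0.736 to 0.770.

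**2. Expected loss.** (60 − 55)/60 = 8.3%.

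**3. Precision.** Assumptions, not in the article: equal correlation ρ between all visits, outcome SD of 1 at each visit, 55/2 = 27.5 per arm with a final score, and the remaining 2.5 per arm seen through month 6.

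- Change score, available cases: SE = √[2(1 − ρ) × 2/27.5]. At ρ = 0.5 this is √(1 × 0.0727) = 0.270.
- Baseline-adjusted (ANCOVA), available cases: SE = √[(1 − ρ²) × 2/27.5]. At ρ = 0.5 this is √(0.75 × 0.0727) = 0.234.
- All-visit likelihood model: SE from the generalised least squares information matrix, with a common baseline mean, arm-specific means at 3, 6 and 9 months, and the covariance treated as known.

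| Assumed ρ | Change score | ANCOVA | All visits | Reduction, change score to all visits |
|---|---|---|---|---|
| 0.3 | 0.319 | 0.257 | 0.256 | 20% |
| 0.5 | 0.270 | 0.234 | 0.232 | 14% |
| 0.7 | 0.209 | 0.193 | 0.191 | 9% |

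At ρ = 0.5 the total gain is 0.270 − 0.232 = 0.038, of which 0.270 − 0.234 = 0.036 comes from baseline adjustment. The interim visits add about 0.002.

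**4. Bias by simulation.** Assumptions: 30 per arm, correlations of 0.50 to 0.65, no true effect, and treatment-as-usual (TAU) participants with a poor 6-month score more likely to miss the final visit. Two implementations were used. The first approximates the mixed model by regression on all visits, and the second uses the likelihood estimator for monotone dropout.

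| Loss | Change t test | ANCOVA, available cases | All data, baseline-adjusted |
|---|---|---|---|
| About 5 lost | −0.01; −0.02 SD | −0.04; −0.06 SD | 0.00; 0.00 |
| 27% of TAU (about 8 of 30) | −0.03; −0.03 SD | −0.10; −0.09 SD | 0.00; 0.00 |

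The SE of the change t test with about 5 lost was 0.268 and 0.274, so its bias is 0.01/0.268 = 4% to 0.02/0.274 = 7% of one standard error.

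**5. How large the bias could be.** Suppose that the lost participants' mean change differs by k SD from the mean change of those retained in the same arm. If all 5 losses fall in one arm, the full-sample contrast moves by k × 5/30: 0.08, 0.17 and 0.25 SD for k = 0.5, 1.0 and 1.5. With a 3/2 split and the same direction in both arms it moves by k × (3 − 2)/30: 0.02, 0.03 and 0.05 SD. With a 3/2 split in opposite directions it again moves by k × 5/30. All values of k are assumed.

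**The case against.** The strongest reply is that this is a pilot. The article limits itself to exploratory testing, names feasibility and acceptability as its main goal, and gives the small sample as its reason for a simple method. The expected loss is disclosed, earlier studies by the team retained 90%, and a statistical analysis plan that is not shown may deal with missing final scores. All of this stands, and it keeps the point modest. It does not remove the mismatch, because the article names the derived variable, the test and the worked contrast. The point rests on that stated method, not on silence about missing data.

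A reader might infer more than the documents support:

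- *That program dropouts are excluded.* They are not. The aim 2 section continues data collection on them, so those still interviewed are analysed in their assigned arm. Only people without a final assessment fall out.
- *That the comparison will be materially biased.* At the expected loss the simulated bias is 4% to 7% of a standard error. The article does not state differential loss. Cornerstone contact is weekly, but no TAU contact frequency is given, and the tracking procedures are described for participants in general.
- *That ignoring the interim scores costs much precision.* They add almost none. The gain comes from baseline adjustment.
- *That the alternative has been shown to be unbiased.* Its zero bias is built in, because simulated loss depended only on an observed score. Loss that depends on the unseen 9-month state was not simulated.

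**Conclusion.** The point holds as one of labelling and efficiency. The stated test is an available-case comparison, by assigned arm, of about 55 of 60 participants. It is not an analysis of all randomised, and it is less precise than the collected data allow. Under equal correlations of 0.7 to 0.3 between visits, a baseline-adjusted all-visit model cuts the standard error of the 9-month contrast by about 9% to 20%, nearly all of it through baseline adjustment.

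The bias from the missing final scores is probably small at 8.3% loss. It becomes appreciable only if losses concentrate in one arm, or run in opposite directions in the two arms, and those lost differ strongly from those retained. The interim visits still have a purpose. In the simulations, baseline adjustment of the available cases alone was somewhat more biased than the change score, and using all visits removed that bias when loss depended on the 6-month score. These sizes rest on assumed correlations and loss mechanisms. The labelling conclusion rests on the article's text alone.

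**What to change.** For the continuous scales measured at all four visits, replace the change-score t test with a repeated-measures model of the 3-, 6- and 9-month scores. Fixed effects are arm, visit, arm × visit, baseline score and baseline × visit, with correlation within person allowed for. Include all randomised participants with any follow-up, in their assigned arm. Report the 9-month arm difference with its 95% CI as exploratory.

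Keep the t test as a sensitivity analysis and call it available-case by assigned arm. State how many participants each analysis includes: someone with a baseline score only does not contribute to the repeated-measures model either, so that model should not be described as covering all 60 unless it does.

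Cost: revised wording and a little more modelling in a small sample, with no new data. The model relies on final scores being missing at random given the observed scores, and the report should say so. If the team prefers to keep the t test as the main analysis, the minimum change is to correct the label.
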